### Interim analysis and stopping rules

No interim analyses of trial outcomes are planned.

### Assessment of harm

On rare occasions, children or schools may need to discontinue the randomised intervention. This may, in most cases, be only a temporary withdrawal, for example, if a child injures themselves with a spade. Minor adverse reactions would not be grounds for discontinuing. However, these events will be captured by either the RHS advisor for the intensive interventions schools, or by the Nutritional Epidemiology Group team through the process measures email for the less intensive schools. All adverse events will be reported to the annual Trial Steering Committee meetings. However, the same procedures would apply as for school or individual withdrawal detailed above. Children who have been withdrawn from the trial due to an adverse reaction of some sort (eg. allergy etc.) will be followed up for 3 months by the study team after withdrawal to assess their condition.

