### Process measures

Process evaluations are useful to identify adherence level to the intervention for each school. At baseline and follow-up, schools will be asked a set of gardening questions which are based on the RHS school bench marking system that ranks schools on their gardening activity levels from 1–5. An email consisting of different questions about gardening activities within the school, will be sent to the class teacher to capture what fruit and vegetables each school grows and harvests. This information will be captured via email in October 2010 for trial year one and October 2011 for trial year two. For the intense intervention trial schools in trial one, additional details regarding the intervention activities within each school will be captured by the regional advisor. For the less intense intervention, level of involvement in the twilight sessions for both trials one and two will be recorded. The regional advisor will keep a record of teacher’s attendance. The nature of this type of intervention allows schools to naturally tailor it to their individual needs. By monitoring what activities are undertaken in the school garden and in the classroom, there is an opportunity to explore how intervention elements might be associated with dietary change.

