### Study interventions

The RHS Campaign for School Gardening consists of two programmes. For the intensive intervention the schools known as Partner Schools receive the following:

· A day visit from the RHS regional advisor each half term to work in the garden with teachers and children (Summer Term 2010 to Summer Term 2011 inclusive).

· Follow up visits to aid lead teachers with planning (Autumn Term 2010 to Autumn Term 2011)

· General ongoing advice on the school garden, free seeds and tools

· 1 twilight teacher training session each term (Summer term 2010 to Summer term 2011 inclusive), based on seasonal tasks in the school garden (open to Partner School teachers and others from local schools)

· Free access to a wide range of teacher resources at http://www.rhs.org.uk/schoolgardening/

The role of the regional advisor is to assist the schools to develop a successful garden, through working directly with teachers and pupils to give them support and practical advice. They are also charged with helping schools overcome particular barriers to developing gardening within schools. Regional advisors have the expertise and experience to tie in gardening and growing activities with the National Curriculum and to run staff training sessions for teachers.

The less intensive intervention schools known as Associate Schools will work with the RHS by attending twilight training once a term at their nearby Partner school, to help support them in developing and using their school garden. Unlike the Partner Schools the Associate schools will not have direct support from the regional advisor. The regional advisor will be running these twilight sessions for them and provide the Associate Schools with advice as needed for their school garden.

Trial One consists of schools participating in both intervention groups mentioned above, whereas for Trial Two schools involved in the less intensive intervention/Associate Schools and a group of control schools are included. These control schools will not receive any support from the regional advisor during the period of the trial, they will however, be eligible for associate intervention at the end of the study. However, it is recognised that most schools will be engaging in some activity around this topic. Baseline evaluation of all schools will assess the level of active engagement with growing by these schools.

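### Adverse events that do not lead to withdrawal are collected by a different route in each arm, with no stated route for comparison schools, so counts by arm would partly reflect how they were collected

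*Protocol article*

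**What the plan says.** Under Assessment of harm, events are to be "captured by either the RHS advisor for the intensive interventions schools, or by the Nutritional Epidemiology Group team through the process measures email", and the email route is limited to one group: "through the process measures email for the less intensive schools". Comparison schools are not mentioned. The same section sends all adverse events to the annual Trial Steering Committee meetings, applies the school and child withdrawal procedures to discontinuations, and follows children withdrawn for a reaction for 3 months.

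Process measures gives the dates of the email: "This information will be captured via email in October 2010 for trial year one and October 2011 for trial year two". It describes the purpose of the email as "to capture what fruit and vegetables each school grows and harvests".

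Under Study interventions, Partner (intensive) schools receive "A day visit from the RHS regional advisor each half term to work in the garden with teachers and children", from Summer Term 2010 to Summer Term 2011. Of the comparison schools it says: "These control schools will not receive any support from the regional advisor during the period of the trial". It also accepts that "it is recognised that most schools will be engaging in some activity around this topic".

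**The concern.** A count of harms by arm can be interpreted only if events have a similar chance of being recorded in each arm. Here the person recording, the means and probably the frequency all change with allocation. In Trial 1 a higher count in intensive schools could be a real excess, or simply closer contact with an advisor on site. In Trial 2 minor events have a stated route in one arm and none in the other. Ordinary garden injuries or reactions in less intensive schools could then be read as caused by the Campaign, although comparison schools may garden too. What is at stake is the harm information that reaches the Trial Steering Committee and any later account of safety by arm. Dietary results are not involved.

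**Working it through.** The protocol states no harm rate or capture figure, so there is nothing of its own to reproduce. The check sets the sections side by side and then illustrates the possible size.

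**Stated route by arm, events not leading to withdrawal**

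| Group | Schools | Collector | Stated occasion |
|---|---|---|---|
| Trial 1 intensive | 10 | RHS advisor | not stated |
| Trial 1 less intensive | 16 | study team, by email | October 2010, October 2011 |
| Trial 2 less intensive | 16 | study team, by email | October 2010, October 2011 |
| Trial 2 comparison | 16 | none stated | none stated |

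The numbers of schools come from the Trial 1 and Trial 2 recruitment sections, the collectors from Assessment of harm, and the dates from Process measures. Within each trial the two arms differ.

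**Events leading to withdrawal.** The School withdrawal and Child withdrawal sections do not distinguish arms. A parent's request reaches the study team whichever group the school is in. This subset therefore has a common route, but Assessment of harm says minor reactions are not grounds for discontinuing, so they would not normally pass through it.

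**Opportunity to record.** Summer 2010, Autumn 2010, Spring 2011 and Summer 2011 make 4 terms. With 2 half terms per term, 4 × 2 = 8 advisor day visits per intensive school, against 2 emails, the second looking back about 12 months. This shows opportunity only: the protocol does not say that the advisor records events at those visits.

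**Illustrative size in Trial 1.** If the true event rate is λ in both arms and a fraction c of events is captured, the observed rate is cλ. The apparent rate ratio is then c(intensive) / c(less intensive), whatever λ is. Assume 80% capture by the advisor and vary capture by email:

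- email 60%: 0.80 / 0.60 = 1.33
- email 40%: 0.80 / 0.40 = 2.0
- email 20%: 0.80 / 0.20 = 4.0

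All of these fractions are assumptions; none comes from the protocol.

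**Trial 2.** No ratio can be given for events that do not lead to withdrawal, because no capture fraction can be attached to an arm without a stated route.

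**The case against.** The strongest reply is that the protocol plans no comparison of harms between arms. Harm is neither a primary nor a secondary outcome, and no harm analysis appears in the statistical sections. The only stated uses are reporting to the Trial Steering Committee and following up withdrawn children. Serious discontinuation is expected to be rare. Comparison schools have no RHS intervention to discontinue, and a condensed article may leave operational detail to a fuller document. The email is described as concerning each school, so it may already reach every arm.

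Much of this stands, and it limits the point. Several stronger readings are tempting but not supported:

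- **That harms cannot be compared at all, or that the comparison arm must show zero events.** Withdrawal-related events can surface from any arm.
- **That a harms table is required and would be biased.** Compliance with good practice mentions CONSORT presentation, a flowchart and intraclass correlations, but no harms table.
- **That capture contacts are 8 to 2 to 0.** The advisor's recording schedule is not given. Less intensive schools also meet the advisor at termly twilight sessions and can ask for advice.
- **That the email contains no harm question.** Its description mentions none, but Assessment of harm relies on it for that purpose.

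The reply does not remove the core. The article does more than omit detail: it states a rule that assigns the collector by arm, and it ties the use of the email for harms to less intensive schools. Even without a formal test, a committee that receives the counts will read them by group.

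**Conclusion.** The point holds in limited form. Followed as written, the plan records adverse events that do not lead to withdrawal differently across the randomised arms of both trials, and states no route for them in the 16 comparison schools. Counts of such events by arm should not be taken as evidence for or against harm from the Campaign.

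The direction in Trial 1, towards more recorded events in intensive schools, rests on the reasonable assumption that an advisor on site catches more than a yearly email. The range of about 1.3 to 4 only illustrates what such a gap could produce and is not an estimate. This deserves correction because events not recorded at the time are hard to recover later, but it does not threaten the trials' main conclusions on diet.

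**What to change.** Add the same short set of adverse-event questions to the process measures email and send it, at the same times, to every school in both trials, comparison schools included. State in Assessment of harm that any account of harms by arm will use this common source only. List events noticed by the advisor separately, labelled as additional and non-comparative, so that nothing seen on site is lost.

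The cost is a small extra burden on class teachers, who would answer a few more questions in an email the study team already sends. If that email does not yet go to comparison schools, it must be extended to those 16. No new staff or procedure is needed.

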### Child withdrawal

A parent may request that an individual child is no longer part of the trial. This request may go either to the school, the RHS or the study team at the University of Leeds. Whoever is the first point of contact with the parent must inform the other relevant groups (school/RHS/University of Leeds) by telephone or letter; this will be recorded in the database. On receipt of this information the study team will send a letter to inform the class teacher that the child is to be withdrawn from the study. A data collection form and freepost envelope will be sent via the class teacher to the parent. A covering letter will make clear to the parent that while the child will not receive any questionnaire for completion, the child will not be left out of whole class activities as to do so would involve taking the child out of the class whilst these activities were occurring.

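### In the less intensive schools, an adverse event that leads to no notified withdrawal has no stated reporting route except an email dated October 2010 and October 2011

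*Protocol article*

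**What the plan says.** Assessment of harm gives a different capture route for each programme. For Partner Schools, "these events will be captured by either the RHS advisor for the intensive interventions schools". For Associate Schools, events are captured "by the Nutritional Epidemiology Group team through the process measures email for the less intensive schools". For oversight, "All adverse events will be reported to the annual Trial Steering Committee meetings".

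Process measures describes the email as a set of questions to the class teacher about gardening activities, "to capture what fruit and vegetables each school grows and harvests". It fixes the timing: "This information will be captured via email in October 2010 for trial year one and October 2011 for trial year two". Adverse events are not among the listed contents.

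Two further statements limit the point. Assessment of harm says that "the same procedures would apply as for school or individual withdrawal detailed above", and under Child withdrawal: "Whoever is the first point of contact with the parent must inform the other relevant groups (school/RHS/University of Leeds) by telephone or letter". That notice is recorded in the database and is not tied to October. The safety follow-up applies to children withdrawn because of an adverse reaction, who "will be followed up for 3 months by the study team after withdrawal to assess their condition".

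**The concern.** The Child withdrawal notice starts when a parent asks that the child leave the trial. School withdrawal starts when a school wishes to leave. Assessment of harm itself expects most discontinuations to be temporary (its example is an injury with a spade) and says that minor reactions are no ground for discontinuing. So the events that the protocol regards as usual need set off neither procedure. In the less intensive schools the only route left for them is a question put to a teacher once a year, in an email not described as asking about harm.

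Three things are at stake. Events would be learnt late, and some would be forgotten over a recall period of up to a year. An event in the 2011 season would reach the study team only after the last stated training sessions, and the committee only at a later annual meeting. In Trial 1, capture would also be uneven: the advisor visits Partner Schools every half term, while Associate Schools rely on annual recall. A simple comparison of event counts between the arms would then partly reflect how closely each arm was observed.

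**Working it through.** The protocol gives no figure for reporting delay, so there is none to reproduce. The check sets its dates side by side and computes the lag from event to email.

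**Schools on the email route.** Sampling and recruitment gives 10 intensive and 16 less intensive schools in Trial 1, and 16 less intensive schools in Trial 2. Less intensive: 16 + 16 = 32. Receiving either programme during the trial: 10 + 32 = 42.

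**Dates in the protocol.** Emails: October 2010 and October 2011. Twilight sessions: Summer Term 2010 to Summer Term 2011 (Study interventions). Growing seasons: those including the summers of 2010 and 2011 (Assessment and follow up). Final data collection: October 2011 (School withdrawal).

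**Assumptions, not in the protocol.**
- Exposure starts on 15 April 2010.
- Exposure ends on 22 July 2011, or on the day of the second email.
- The email goes out on 1, 15 or 31 October.
- Events are equally likely on every day of one of four sets: all calendar days; days within assumed term dates; April to September days; April to September days within term.

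This makes 3 × 2 × 4 = 24 scenarios.

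**Formulas.** Lag = date of the next email − date of the event. Late share = days with a lag above 91 days ÷ all days in the set. Months = days ÷ 30.4.

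**One scenario in full** (calendar days, email on 15 October, exposure to 22 July 2011):
- 15 April to 15 October 2010: 184 days. A lag above 91 days means an event up to 15 July 2010, which is 92 days.
- 16 October 2010 to 22 July 2011: 280 days. A lag above 91 days means an event up to 15 July 2011, which is 273 days.
- Late share = (92 + 273) ÷ (184 + 280) = 365 ÷ 464 = 79%.
- Longest lag: 16 October 2010 to 15 October 2011 = 364 days, or 12.0 months.

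**All scenarios** (range over the three email dates and two end dates):

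| Days on which events can fall | Late share | Mean lag (months) | Longest lag (months) |
|---|---|---|---|
| Calendar days | 66–80% | 5.0–5.8 | 12.0 |
| Term days | 74–85% | 5.2–5.9 | 12.0 |
| April–September, all days | 48–78% | 2.9–4.3 | 6.0–7.0 |
| April–September, term days | 60–87% | 3.1–4.4 | 5.6–6.5 |

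The late share exceeds one half in 23 of 24 scenarios. The exception takes all April to September days, an email on 1 October and exposure counted to that date: (78 + 92) ÷ (169 + 183) = 170 ÷ 352 = 48%.

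**The 2011 season.** Any event after the October 2010 email is next asked about in October 2011. If Summer Term ends on 22 July 2011, that is 71 days (1 October) to 101 days (31 October) after the last term with a stated twilight session, or about 2 to 3 months.

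The 91-day threshold is only a yardstick for lateness. It does not measure missed safety follow-up.

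**The case against.** The strongest case against is that the email is not the only route. Assessment of harm applies the withdrawal procedures, including the telephone or letter notice, and describes a brief stop as a temporary withdrawal. On that reading an interruption already triggers notice, and the email merely collects minor events for an annual summary. For school gardening, with discontinuation expected only on rare occasions, that could be proportionate. This is also a condensed article, and event forms and expedited reporting rules may stand in a fuller document.

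Part of this stands. A child whose parent asks for withdrawal is notified promptly, so it would be wrong to say that every adverse event waits for October. But the Child withdrawal procedure begins with a parent's request. Even if a temporary stop counts as a withdrawal, nothing stated obliges anyone to report it when no parent asks. The condensed format does not remove the point either, because the article states the route and its dates, and those are what give the delay.

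A reader might infer that the 3-month follow-up is missed for most affected children. The protocol does not support this. That period runs from withdrawal, not from the event, and covers only children withdrawn for an adverse reaction, who come to notice through the withdrawal route.

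A reader might also infer that the programme is over by October 2011 and the committee powerless. That goes too far. Summer Term 2011 is the stated end of the twilight sessions, while Assessment and follow up places the final measures, in Autumn Term 2011, at the end of the intervention. The committee's meeting dates are not given.

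**Conclusion.** The point holds in a limited form. In 32 of the 42 schools receiving a programme, an adverse event with no notified withdrawal has one stated route: an email on two dates a year apart, not described as asking about harm, followed by an annual committee meeting. Such an event can be learnt up to about 12 months later, or up to about 7 months if events fall only between April and September. Between 48% and 87% would be learnt after more than 3 months. These figures rest on assumed term dates, email dates and evenly spread events. The order of the dates does not: events after the October 2010 email are next asked about after the last term with a stated twilight session.

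Severity is low. No outcome, estimate or test in the protocol depends on it, and events are expected to be rare. It is worth correcting because the change is cheap and improves the capture of harm.

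**What to change.** Reconcile Assessment of harm, Child withdrawal and Process measures on how and when events reach the study team:

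- Extend the existing telephone or letter notice, and its database record, to any adverse event that interrupts a child's or a school's participation, temporarily or not, with or without a parental request.
- Have the study team pass these events to the steering committee on receipt, and keep the annual meeting for the summary.
- Keep the October email as a check for missed events, and add an explicit adverse-event question to it.
- Leave the 3-month follow-up rule as it is, and ask the sponsor only to clarify to whom it applies.

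The cost is amendment wording, a line in the information given to schools, and a little extra reporting by schools. The notice route and the database record already exist.

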### Randomisation

Cluster randomisation with school location and borough to identify each “cluster” will be used to randomise the schools. The schools will be randomised by their London borough location using Stata[39]. They will be randomly assigned, for trial one to the intense RHS intervention or the less intense RHS intervention; for trial two to the less intense intervention or the delayed intervention (comparison). If the schools had more than one Year 3 or Year 4 class, the same statistical method will be used to determine which class should be involved in the trial.

### Compliance with good practice

· All statistical analyses of primary and secondary trial outcomes will be carried out under the guidance of the trial statistician.

· CONSORT guidelines will be followed for presentation of results from cluster randomised trials [40]

· Presentation of results will conform to good practice for presentation of trials of complex interventions[41].

· The flow of both clusters and individuals through the trial, from assignment to analysis, will be presented using a flowchart, in accordance with CONSORT guidelines [40].

· Intraclass correlation coefficients from the multilevel analyses will be presented following good practice for cluster randomised trials.

### Ethical considerations

Ethical approval was obtained through the Leeds Institute of Health Sciences and Leeds Institute of Genetics, Health and Therapeutic joint ethics committee (Reference number: 09/012). Written informed consent from all schools will be obtained first and then obtained from all parents whose children are in the classes chosen to participate in the trial data collection. Schools and parents will be informed about the potential risks and benefits of participating in the trial through the information sheet. Participant’s parents will be given informed consent, with the opportunity to “opt-out” of the study if they did not wish their child to take part. If the parents wished their child not to participate in the study, they will still able to take part in the growing activities; however their food intake and child attitude and knowledge questionnaire will not be recorded.

